## LIST OF ABBREVIATIONS AND RELEVANT DEFINITIONS

|                |                                                                                                                                                                                                                                                                                                                                                  |
|----------------|--------------------------------------------------------------------------------------------------------------------------------------------------------------------------------------------------------------------------------------------------------------------------------------------------------------------------------------------------|
| ABR     | General Assessment and Registration form (ABR form), the application form that is required for submission to the accredited Ethics Committee; in Dutch: Algemeen Beoordelings- en Registratieformulier (ABR-formulier)                                                                                                                    |
| AE      | Adverse Event                                                                                                                                                                                                                                                                                                                             |
| AR      | Adverse Reaction                                                                                                                                                                                                                                                                                                                          |
| CA      | Competent Authority                                                                                                                                                                                                                                                                                                                       |
| CCMO    | Central Committee on Research Involving Human Subjects; in Dutch: Centrale Commissie Mensgebonden Onderzoek                                                                                                                                                                                                                               |
| CV      | Curriculum Vitae                                                                                                                                                                                                                                                                                                                          |
| DSMB    | Data Safety Monitoring Board                                                                                                                                                                                                                                                                                                              |
| EU      | European Union                                                                                                                                                                                                                                                                                                                            |
| EudraCT | European drug regulatory affairs Clinical Trials                                                                                                                                                                                                                                                                                          |
| GCP     | Good Clinical Practice                                                                                                                                                                                                                                                                                                                    |
| GDPR    | General Data Protection Regulation; in Dutch: Algemene Verordening Gegevensbescherming (AVG)                                                                                                                                                                                                                                              |
| IB      | Investigator's Brochure                                                                                                                                                                                                                                                                                                                   |
| IC      | Informed Consent                                                                                                                                                                                                                                                                                                                          |
| IMP     | Investigational Medicinal Product                                                                                                                                                                                                                                                                                                         |
| IMPd    | Investigational Medicinal Product Dossier                                                                                                                                                                                                                                                                                                 |
| METC    | Medical research ethics committee (MREC); in Dutch: medisch-ethische toetsingscommissie (METC)                                                                                                                                                                                                                                            |
| (S)AE   | (Serious) Adverse Event                                                                                                                                                                                                                                                                                                                   |
| SPC     | Summary of Product Characteristics; in Dutch: officiële productinformatie IB1-tekst                                                                                                                                                                                                                                                       |
| Sponsor | The sponsor is the party that commissions the organisation or performance of the research, for example a pharmaceutical company, academic hospital, scientific organisation or investigator. A party that provides funding for a study but does not commission it is not regarded as the sponsor, but referred to as a subsidising party. |
| SUSAR   | Suspected Unexpected Serious Adverse Reaction                                                                                                                                                                                                                                                                                             |
| UAVG    | Dutch Act on Implementation of the General Data Protection Regulation; in Dutch: Uitvoeringswet AVG                                                                                                                                                                                                                                       |
| WMO     | Medical Research Involving Human Subjects Act; in Dutch: Wet Medisch-wetenschappelijk Onderzoek met Mensen                                                                                                                                                                                                                                |

## SUMMARY

**Rationale:** Every year, about 40,000 people in the Netherlands have a stroke. After the initial admission to the hospital, about 15% of stroke survivors is admitted to a rehabilitation center because of remaining disabilities. Three out of four of these patients have upper limb dysfunction, hampering activities of daily living. Upper limb function plays a critical role in the performance of most daily life activities. In our phase II trial B-STARS, continuous theta burst stimulation (cTBS) treatment, a form of repetitive transcranial magnetic stimulation (rTMS), led to an absolute additional recovery of upper limb function of 17%, as measured with the Action Research Arm Test (ARAT) score three months after stroke. This improvement exceeds the minimal clinically important difference of 10%. cTBS treatment also resulted in a significant improvement in measures of activities and participation (of similar magnitude) and a reduction in the mean length of stay at the rehabilitation center by 18 days.

**Objective:** To assess the effectiveness and cost effectiveness of cTBS treatment in promoting upper limb recovery after stroke in patients admitted to a rehabilitation center.

**Study design:** A phase III, multi-center, double-blind, randomized, sham-controlled, clinical trial.

**Study population:** 454 patients aged 18 years or older with a first-ever ischemic stroke or intracerebral hemorrhage and a unilateral arm paresis, defined by a Motricity Index between 9 and 99, in whom cTBS treatment can be started within 3 weeks after stroke onset.

**Intervention:** 10 daily sessions of cTBS delivered over the contralesional primary motor cortex during a period of 2 weeks, immediately before regular care physical therapy of the affected upper limb.

**Main study parameters/endpoints:** The primary endpoint will be the score on the upper extremity section of the Fugl-Meyer assessment (FM-UE) at 90 days after stroke. Secondary endpoints will include the score on the FM-UE at one year and the scores on the Action Research Arm Test, Nine Hole Peg Test, Stroke Impact Scale, EuroQol 5 Dimensions and modified Rankin Scale at 90 days and one year after stroke

**Nature and extent of the burden and risks associated with participation, benefit and group relatedness:**

Data from our phase II trial B-STARS indicate that cTBS treatment results in 17% additional recovery of upper limb function, as measured with the ARAT at three months after stroke. This additional recovery led to a significant improvement in the activity and participation domain (of similar magnitude) and a reduction in the length of stay at the rehabilitation center by 18 days on average. Risks associated with active cTBS were limited to headache (<4%) and muscle pain (<1%). Analysis of interviews with a selected number of patients showed that cTBS was well tolerated.

## 1. INTRODUCTION AND RATIONALE

Every year about 40,000 people in the Netherlands have a stroke. Despite advances in the treatment of stroke in the acute phase, most patients experience lasting disability, including persistent impairments in upper limb function, hampering activities of daily living, societal participation and quality of life. There is no proven effective treatment for these persistent impairments. In recent years, non-invasive brain stimulation techniques, such as repetitive transcranial magnetic stimulation (rTMS), have shown promise as a therapeutic means to promote functional recovery after stroke.

In 2022, our team completed a phase II, single-blinded, mono-center randomized controlled trial of rTMS in sixty stroke patients at rehabilitation center De Hoogstraat. In this trial a specific rTMS protocol, involving continuous theta-burst stimulation (cTBS), started within three weeks after stroke, improved upper limb function up to at least one year after stroke. The treatment was safe and well-tolerated and was associated with a reduction in the duration of admission to the rehabilitation center by a mean of 18 days. These findings corroborate results from systematic reviews and meta-analyses of published studies, suggesting benefit of rTMS on upper limb function if started within the first month after stroke. Because our trial was a relatively small ( $n = 60$ ) single-center study and the methods and results of the trials included in abovementioned meta-analyses were heterogeneous, these findings are insufficient to change clinical practice. In a recent module of the Dutch guideline 'Ischemic stroke and intracerebral hemorrhage', it is concluded that inhibitory rTMS in the first weeks after stroke is a promising treatment for improvement of upper limb function, but that this needs to be tested in high-quality phase III trials before rTMS can be recommended as a standard of care.

We therefore propose a multicenter, randomized, controlled, phase III clinical trial of cTBS for upper limb recovery after stroke across multiple rehabilitation centers in the Netherlands. Therapeutic efficacy will be measured with the Fugl-Meyer Upper Extremity test at 90 days and one-year post-stroke. Additionally, cost effectiveness will be assessed by a healthcare technology assessment expert. If the treatment is proven effective, implementing rTMS in rehabilitation therapy can improve functional recovery in thousands of stroke patients in the Netherlands annually. Moreover, a proven effective treatment would likely result in significant cost savings due to shorter duration of admission to a rehabilitation center and faster societal integration.

## 2. OBJECTIVES

Primary Objective:

- To assess whether 10 sessions of cTBS of the contralesional primary motor cortex (M1) combined with regular care upper limb training, started within three weeks after stroke onset and continued every working day for two weeks, reduces upper limb impairment at 90 days after stroke, compared to sham stimulation.

Secondary Objective(s):

To assess whether 10 sessions of cTBS of the contralesional M1 combined with regular care upper limb training, started within three weeks after stroke onset and continued every working day for two weeks:

- improve upper limb activity, manual dexterity and quality of life, and reduces disability and dependence at 90 days and 12 months after stroke, compared to sham stimulation;
- reduce upper limb impairment at 12 months after stroke, compared to sham stimulation;
- are cost-effective compared to sham stimulation;
- reduce excitability of the contralesional M1 during the 2-week treatment period, compared to sham stimulation;
- increase ipsilesional M1 excitability after 10 treatment sessions, compared to sham stimulation.

## 3. STUDY DESIGN

We will perform a multi-center, double-blind, randomized, sham-controlled, clinical trial. Subjects will be recruited from multiple rehabilitation centers in the Netherlands over a period of 51 months (Q2 of 2024 to Q4 of 2028). The total duration of follow-up for each participant is until one year after stroke. The total study duration is 63 months.

Baseline assessment will be performed before the start of the intervention, which must occur within 21 days after stroke onset. Follow-up assessments will be performed at 90 days (+/- 7 days) and 12 months (+/- 14 days) post-stroke (Figure 1). Outcome assessments are described in Table 1 and will be described in more detail in section 8.3.

[figure not shown]

**Figure 1.** Study timeline.

**Table 1.** Outcome assessments

| Assessment                          | Timepoint                              | Description                                 | Abbreviation |
|-------------------------------------|----------------------------------------|---------------------------------------------|--------------|
| Fugl-Meyer – Upper Extremity        | Baseline, 90 days
12 months         | Upper extremity impairment test             | FM-UE        |
| Action Research Arm Test            | Baseline, 90 days
12 months         | Upper extremity activity test               | ARAT         |
| Nine Hole Peg Test                  | Baseline, 90 days
12 months         | Manual dexterity test                       | NHPT         |
| Modified Rankin Scale               | Baseline, 90 days
12 months         | Disability and dependence questionnaire     | mRS          |
| Barthel Index                       | Baseline, 90 days
12 months         | Activities of daily living questionnaire    | BI           |
| Stroke Impact Scale – Hand          | Baseline, 90 days
12 months         | Hand function questionnaire                 | SIS-hand     |
| Stroke Impact Scale - participation | Baseline, 90 days
12 months         | Participation questionnaire                 | SIS-par      |
| EuroQol - 5 dimensions              | Baseline, 90 days, 6 months, 12 months | Quality of life questionnaire               | EQ-5D-5L     |
| Length of stay                      |                                        | Length of stay in the rehabilitation center | LOS          |

|                             |                                                                                          |                                                                                                  |      |
|-----------------------------|------------------------------------------------------------------------------------------|--------------------------------------------------------------------------------------------------|------|
| Contralesional excitability | Before the first, 6 th and 10 th cTBS session                      | Resting motor threshold of the contralesional M1                                                 | cRMT |
| Ipsilesional excitability   | Before the 1 st cTBS session and after the 10 th cTBS session.     | Resting motor threshold of the ipsilesional M1                                                   | iRMT |
| Contralesional inhibition   | Before and after the 1 st , 6 th and 10 th cTBS session | Ratio between the average motor-evoked potential amplitude before and after cTBS.                | CI   |
| TMS disruption              | Baseline                                                                                 | Change in tapping frequency of the affected hand during disruption of contralesional M1 activity |      |

## 4. STUDY POPULATION

### 4.1 Population (base)

Every year, some 3,000 stroke patients are admitted to clinical rehabilitation programs across rehabilitation centers in the Netherlands (Vektis declaratieset MSR 2020). 75% of whom experiences loss of upper limb function and may be eligible for inclusion in our trial. 454 of these patients will be recruited from rehabilitation centers in the Netherlands.

### 4.2 Inclusion criteria

To be eligible to participate in this study, a participant must meet all the following criteria:

- Age, 18 years or older
- First-ever unilateral ischemic stroke or intracerebral hemorrhage in a cerebral hemisphere or in the brainstem;
- Unilateral upper limb paresis with a motricity index between 9 and 99;
- Possibility to start cTBS treatment within 21 days after stroke onset;
- Signed informed consent.

### 4.3 Exclusion criteria

A potential subject who meets any of the following criteria will be excluded from participation in this study:

- Upper limb paresis prior to stroke onset;

- Absolute contra-indication to TMS
  - Magnetically sensitive objects implanted in or guided through the head or neck area (e.g. cochlear implants, implanted neurostimulator, pacemaker or defibrillator leads, metal splinters, metal fragments or metal clips) with the exception of dental work (e.g. fillings, braces or implants);
  - History of epilepsy;
  - Pregnancy;
  - Other contra-indications that may potentially be harmful as determined by the treating rehabilitation physician;
- Incapacity or severe impairments (i.e. extreme fatigue, major communication deficits) that can impede study participation as determined by the treating rehabilitation physician;
- Life expectancy shorter than one year.

#### 4.4 Sample size calculation

The required sample size to test our hypothesis (superiority) in two groups is 440 subjects, based on a two-sided two-sample t-test power calculation with a minimal detectable effect of 6.6 points on the FM-UE scale (10% of the maximum score of 66, a mean score at 90 days of 42 and a standard deviation of 23 (calculated from the B-STARS trial data), a statistical significance level of 0.05 and statistical power of 0.85 (G\*power 3).

A study that specifically examined clinically important differences of FM-UE scores in stroke patients found that these ranged from 4.25 to 7.25 points, depending on the different facets of UE movement. A minimal clinically important difference of 6.6 points (10% of the maximum score FM-UE score) is in line with the module 'Noninvasive brain stimulation with rTMS' for the Dutch guideline 'Ischemic stroke and intracerebral hemorrhage'.

To compensate for possible loss to follow-up, we will include 454 patients. This sample size is also sufficient to demonstrate a treatment effect on secondary outcome measures. For example, for the ARAT, which tests upper limb-specific activity, a sample size of at least 396 would be required, based on a minimal clinically important difference of 5.7 and a mean score and standard deviation of 30 and 23, respectively (calculated from the B-STARS trial data), a statistical significance level of 0.05, and a statistical power of 0.8 (gigacalculator.com).

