#### **6.4 Summary of known and potential risks and benefits**

Data from our phase II trial (B-STARS) shows that cTBS treatment leads to a clinically relevant improvement in upper limb recovery, with 17% (n 60; 9.6 points; 95%CI 1.2–17.9) additional recovery of upper limb activity, as measured with the ARAT score three months after stroke. This additional recovery led to a significant improvement in the activity and participation domain (of similar magnitude) of the International Classification of Functioning, Disability and Health (ICF) model, and a reduction in the length of stay at the rehabilitation center by 18 days on average. These findings corroborate results from a systematic review and meta-analysis of published studies, revealing benefit of rTMS on upper limb function if started within the first month after stroke.

The most serious adverse effect is the occurrence of a seizure at a crude risk of approximately 0.02% per stimulation session, as reported in a systematic review of 67 studies with 1,040 subjects and >4,500 sessions. More common adverse events during and after TBS are transient headache and neck pain, reported by <3% of subjects. CTBS treatment did not lead to seizures in our phase II trial. We only observed mild side effects, such as headache (<4%) and muscle pain (<1%) and the intervention was reported to be tolerable and comfortable.

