## 2. Study design

B-STARS2 is a multi-centre, double-blind, randomised, sham-controlled, clinical trial.

Participants will be recruited from 16 rehabilitation centres in the Netherlands over a period of 51 months (Q2 of 2024 to Q4 of 2028). The total duration of follow-up for each participant is until one year after stroke. The total study duration is 63 months.

Baseline assessment will be performed before the start of the intervention, which must occur within 21 days after stroke onset. Follow-up assessments will be performed at 90 days (+/- 7 days) and 12 months (+/- 14 days) post-stroke (Figure 1).

The intervention consists of ten daily sessions of active or sham cTBS, delivered over the contralesional primary motor cortex, started within 21 days post-stroke and combined with regular care upper limb therapy.

Participants are randomly assigned in a 1:1 ratio to one of the two treatment groups (group A or B) using a web-based data management service. Treatment allocation is stratified by rehabilitation centre and the ability to extend one or more fingers of the affected hand.

An independent DSMB is monitoring the safety of participants of the trial. The DSMB meets at least annually. An independent statistician will perform unblinded interim analyses on all reported (serious) adverse events after 150 and 300 patients have completed the 90 days post-stroke follow-up. The independent statistician will report the outcome of the interim analyses directly to the DSMB, as well as listings of all SAE reports and unblinded aggregate summaries of data by treatment group for review in closed meetings. Feedback, blind to treatment, will be provided in written conclusions to the B-STARS2 project leaders.

[figure not shown]

**Figure 1.** Study timeline.

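### Protocol 4.4: the ARAT figure of 396 does not follow from its stated inputs under the two-sided t-test used for the primary endpoint (514), so it does not support the claim that 454 patients suffice

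*Combined protocol and SAP*

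**What the plan says.** Protocol section 4.4 first sizes the trial on the Fugl-Meyer upper extremity score (FM-UE). It arrives at a total of 440, a figure it describes as "based on a two-sided two-sample t-test power calculation with a minimal detectable effect of 6.6 points on the FM-UE scale". The other inputs are an SD of 23, α = 0.05 and 85% power. The total is then raised to 454 for loss to follow-up.

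The section goes on: "This sample size is also sufficient to demonstrate a treatment effect on secondary outcome measures". The only support given is an ARAT example, in which "a sample size of at least 396 would be required, based on a minimal clinically important difference of 5.7". The remaining ARAT inputs are a mean of 30, an SD of 23, α = 0.05 and 80% power. The ARAT sentence does not say whether the test is one-sided or two-sided, and it cites a different calculation tool from the primary calculation.

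Allocation is equal (SAP section 2: "Participants are randomly assigned in a 1:1 ratio to one of the two treatment groups"). Protocol section 10.3 and SAP section 7.5 plan to analyse the ARAT with a mixed model that includes the baseline score. Neither announces a one-sided test for the ARAT or any other efficacy outcome.

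**The concern.** Both calculations use an SD of 23. The ARAT calculation targets a smaller difference (5.7 against 6.6 points) and returns a smaller total (396 against 440). The lower power target (0.80 against 0.85) pulls the other way, but not by enough to explain this, so the two figures do not look like products of the same method.

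The sufficiency statement for secondary outcomes rests on this one figure. The ARAT also carries the phase II result that motivates the trial: protocol section 6.4 reports the 17% gain as "additional recovery of upper limb activity, as measured with the ARAT score three months after stroke". A reader who accepts 396 will take it that a 5.7-point ARAT difference can be detected with more than 80% power at 454, and may weigh a non-significant ARAT result accordingly.

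**Working it through.** **Inputs.** From protocol 4.4: ARAT difference 5.7, SD 23, α = 0.05, power 0.80; FM-UE difference 6.6, SD 23, α = 0.05, power 0.85; N = 440, raised to 454. From SAP 2: 1:1 allocation.

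**Formula.** Normal approximation, n per arm = 2 × [SD × (z_α + z_power) / difference]². The exact t-test solution is given beside it.

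**Step 1: reproduce the primary figure.** Two-sided, z = 1.960 + 1.036:
- Normal: 2 × (23 × 2.996 / 6.6)² = 218.1, so 219 per arm, 438 in total.
- Exact t-test: 219.03, so 220 per arm, **440** in total, as stated.
- A one-sided calculation would give 350. The primary calculation is therefore two-sided, as the protocol says.

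**Step 2: the same method for the ARAT.** Two-sided, z = 1.960 + 0.842:
- Normal: 2 × (23 × 2.802 / 5.7)² = 255.6, so 256 per arm, 512 in total.
- Exact t-test: 256.6, so 257 per arm, **514** in total.
- This is not 396, and it exceeds 454 by 60.
- Rounding of the SD does not explain the gap: SD 22.5 gives 490 and SD 23.49 gives 534 (normal approximation).

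**Step 3: what comes near 396.**
- One-sided 5%, z = 1.645 + 0.842: 2 × (23 × 2.487 / 5.7)² = 201.3, so 202 per arm, 404 in total. The exact t-test needs 202.01, so 203 per arm, 406 in total.
- One-sided, normal approximation, effect size 5.7/23 = 0.248 rounded to 0.25: 2 × 2.487² / 0.25² = 197.8, so 198 per arm, 396 in total.
- Two-sided with other inputs: an SD of about 20.2, or a difference of about 6.5, would also give 396. Neither is stated.

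**Step 4: power on the stated inputs** (5.7 points, SD 23, unadjusted t-test).

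| Total N | Two-sided power | One-sided power |
|---|---|---|
| 396 | 69% | 79% |
| 440 | 74% | 83% |
| 454 | 75% | 84% |

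The 440 row corresponds to the loss built into the plan: (454 − 440)/454 = 3.1%. The difference detectable with 80% two-sided power is 6.16 points at 440 and 6.06 at 454, both above 5.7.

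**Step 5: effect of baseline adjustment.** If the baseline score correlates r with the outcome, the residual SD is about 23 × √(1 − r²). The documents give no r, so the values below are assumptions.

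| Assumed r | Power at 440 | Power at 454 | N for 80% (normal approx.) |
|---|---|---|---|
| 0 | 74% | 75% | 512 |
| 0.3 | 78% | 79% | 466 |
| 0.5 | 85% | 86% | 384 |
| 0.7 | 95% | 96% | 262 |

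Two-sided power reaches 80% at r of about 0.38 with 440 patients and about 0.34 with 454.

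**The case against.** The strongest reply is that the trial will not analyse the ARAT with an unadjusted t-test. The planned model includes the baseline score, and a modest correlation restores 80% two-sided power. This stands, and it limits the conclusion. A reader might infer from 514 against 454 that the trial is underpowered for the ARAT and that the sufficiency claim is false. The documents do not support that. They show only that the printed calculation does not establish the claim; section 4.4 neither invokes the adjustment nor gives a correlation.

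Second, the ARAT sentence does not say two-sided. That is true, and under a one-sided 5% test 454 would be enough (84%). However, the section describes its primary calculation as two-sided, and no one-sided efficacy test is planned anywhere. The exact match to 396 in step 3 needs three choices together (one-sided, normal approximation, rounded effect size), and a misprinted SD or difference would also serve. It is tempting to state as fact that the calculation was run one-sided, but the tool's settings are not documented.

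Third, a reader might go the other way and take the phase II interval (1.2 to 17.9, n = 60) as proof of ample power. Its half-width of 8.35 gives 8.35/1.96 = 4.26, and 4.26/√(4/60) = 16.5 as an implied SD, hence about 96% power at 454. This assumes equal arms, all 60 analysed, and a comparable model at a single time point. The protocol documents none of these, so the figure cannot be relied on.

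Finally, this is an illustrative example for one of many secondary outcomes. That stands too, and it bears on severity.

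**Conclusion.** The concern holds in a limited form. On the stated inputs, and with the two-sided t-test that reproduces the primary 440, the ARAT requirement is 514, not 396. The planned size gives about 74% (440) to 75% (454) unadjusted power for 5.7 points, 5 to 6 percentage points short of the stated 80%. The detectable difference is about 6.1 to 6.2 points.

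This rests on one assumption: that the ARAT comparison is two-sided, like the primary calculation. Actual power under the planned adjusted model depends on a correlation the documents do not give, and could be well above 80%.

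The point should be fixed but is not critical. The primary sample size, the randomisation and the planned analyses do not change.

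**What to change.** Revise the ARAT sentences in protocol section 4.4 in one of two ways:

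1. State that the calculation is two-sided, replace 396 with 514, and report that the planned size gives about 74% power (440 evaluable) to 75% (454) for 5.7 points on an unadjusted comparison.
2. Base the statement on the planned baseline-adjusted model. Give the assumed baseline-outcome correlation or residual SD, say where it comes from, and show a range. For example, r of about 0.38 at 440 or 0.34 at 454 gives 80%, and r = 0.5 gives about 85 to 86%. The sponsor holds the phase II data and can estimate this directly.

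In either case, limit the sufficiency statement to the ARAT, the only secondary outcome for which a calculation is shown.

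The cost is one paragraph of protocol text and, under the first option, a slightly less favourable stated power. No extra patients are needed.
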